### Intervention Period

During the 10-week intervention period, participants will continue to wear their Fitbit and complete the same weekly survey (SRBAI and a single-item assessing overall health from the EuroQol EQ-5D-5L) as during the baseline period. Additionally, participants will receive an automated multicomponent BCT intervention package consisting of 7 SMS text messages daily via REDCap (delivered using the Alerts and Notifications application) with 4 BCTs to promote a walking habit of taking an additional 250 steps per hour for the same 4 hours each day.

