### Primary Outcome and Analysis

The primary outcome is a binary indicator of habit formation. The goal is to identify whether a significant proportion of caregivers (≥50%) develop habitual hourly walking, thereby disrupting the time they spend sedentary. A participant will have successfully formed a habit of walking if they attain walking 250 steps each hour during their preidentified, preferred 4-hour period each day for 7 consecutive days during the 70-day intervention period (Figure 6). We used this definition of habit to reflect behavioral consistency in physical activity performance. Consistency of physical activity behavior has been found to be a strong correlate of habit in previous research [84]. To ensure that our definition of habit does not bias results, we will conduct sensitivity analyses using 10-day, 14-day, and 21-day periods in addition to the 7-day period used for our primary outcome. We will use a null hypothesis rate of 30% and will compare the achieved proportion of habit formation versus this null level, using a 1-sample binomial test with a 2-sided α at 5%. The rate of habit formation will be summarized using the observed proportion along with a 95% CI. We will also use Kaplan-Meier curves to identify estimates of the time-to-event for habit formation in the sample.

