### Secondary Outcomes and Analysis

One of the secondary hypotheses of this trial is whether the binary outcome described above of habit formation is associated with positive changes in behavioral automaticity using the SRBAI. Behavioral automaticity is the hypothesized key MoBC for this trial. A Fisher exact test (5%, 2-sided) will be used to examine whether an hourly walking habit formation will be associated with positive changes in behavioral automaticity. Specifically, for each participant, the difference between average behavioral automaticity during the last 2 weeks of intervention and average baseline behavioral automaticity will be calculated; a positive change is defined as a difference of greater than zero. Additionally, we will model the association between habit and continuous changes in automaticity over time using autoregressive models of order 1 to account for serial autocorrelation between repeated measures of the SRBAI. Finally, a mixed-effects logistic regression will be used to assess the effects of behavioral automaticity on the development of a daily walking habit, with adjustment for other factors, such as caregiver demographic characteristics and factors related to caregiving. For this model, we will examine the fixed effects of automaticity, time, and the time-by-automaticity interaction effect to examine whether changes in automaticity over time are associated with habit formation.

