Additionally, another secondary hypothesis of this trial examines the association between longitudinal behavioral automaticity and habit formation over time. These analyses will provide preliminary estimates of how behavioral automaticity changes at a given week impact the attainment of the first operationalization of habit formation, thus informing how the timing of behavioral automaticity change will impact habit. Briefly, the association between habit formation and behavioral automaticity (measured by the SRBAI) at a given week will be assessed first using univariate logistic regression. Then, weekly behavioral automaticity changes will be jointly explored in a multivariable isotonic regression model, which will be analyzed using the R package *McMiso* [85,86]. Briefly, each participant’s achievement of habit formation (binary yes or no) at a given week will be regressed on SRBAI in that week and the week number using multivariable isotonic regression. This analysis will include data up to the first week where a habit is formed; if a habit is not formed, we will use SRBAI data in all 10 weeks. To further assess lagged effects, we will next regress achievement of habit formation on SRBAI in the same week and in the previous week, as well as the week number. A few methodological notes are in order. First, these analyses will include data up to the first week where a habit is formed. For example, if a habit is not formed in a participant, we will use SRBAI data for all 10 weeks. Once a habit is formed, we will not use SRBAI data after the event, so that temporally the dependent outcome is preceded by the independent variables. Second, isotonic regression assumes a monotonic association between habit (dependent variable) and the independent variables (SRBAI and time). This assumption is reasonable because automaticity (as measured by the SRBAI) should increase proportionally as habit formation becomes more likely. Also, since time as a covariate indicates the *cumulative* risk of forming a habit, we also expect the association between habit and week number to be positive. Third, isotonic regression does not impose additional assumptions other than monotonicity, such as linearity as in logistic regression and additivity between covariates, and hence represents a data-driven tool to explore the relationship between habit and SRBAI.

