## Discussion

### Principal Results

This NIH Stage II decentralized behavioral trial has the potential to advance science on forming a habit to disrupt sedentary behavior among caregivers for persons with ADRD and will help determine whether behavioral automaticity acts as the primary MoBC for the effect on this BCT intervention to form an hourly walking habit. If successful, this trial will inform further NIH Stage III effectiveness trials, can be applied to other ADRD populations, and can be applied to other physical activity behaviors, such as moderate activity interventions. Although out of scope for this trial, additional areas of exploration should also include objective confirmation of sedentariness and maintenance of habit formation to understand whether hourly walking habits persist long-term and beyond delivery of the intervention.

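### The weekly automaticity models use same-week SRBAI, which never precedes the 7-day run that defines the habit, so the stated time order does not hold for that term

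*Protocol article*

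**What the plan says.** All references are to the protocol article.

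- **Outcome.** Primary Outcome and Analysis defines the habit as reaching the hourly step target in the chosen 4-hour block "each day for 7 consecutive days during the 70-day intervention period".
- **Automaticity.** Under Intervention Period, participants "complete the same weekly survey (SRBAI and a single-item assessing overall health" as at baseline. The day of the week on which it is completed is not given.
- **Weekly models** (Secondary Outcomes and Analysis, second paragraph). Habit in a given week is "regressed on SRBAI in that week and the week number using multivariable isotonic regression". For lagged effects, the plan is to "regress achievement of habit formation on SRBAI in the same week and in the previous week, as well as the week number". Data run through the first week in which a habit is formed, SRBAI after the event is not used, and the stated purpose is "so that temporally the dependent outcome is preceded by the independent variables".
- **Fisher test** (same section, first paragraph). Habit at any time is compared with whether SRBAI rose, where "the difference between average behavioral automaticity during the last 2 weeks of intervention and average baseline behavioral automaticity will be calculated".
- **Intended reading.** The second paragraph speaks of automaticity changes having an impact on habit attainment. Principal Results says the trial "will help determine whether behavioral automaticity acts as the primary MoBC for the effect on this BCT intervention".

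**The concern.** The outcome takes seven days to accrue and the predictor is a weekly survey. If the survey is taken while the seven days are being walked, or after they are complete, a higher score may be a result of the walking. The protocol's own Introduction describes habit as arising from repetition in a stable context, so this direction is plausible.

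At stake is what the secondary analyses can say. A positive same-week coefficient would be expected whether automaticity drives walking or walking drives automaticity. Because the protocol says its data cut secures the time order, a reader would take that coefficient as evidence for the mechanism.

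**Working it through.** **Plan's own figures.** No figure is attached to the time order. The only related one is the power for the Fisher comparison (60% versus 20% habit, n=60): 86% when 30% have increased automaticity and about 89% when 50% do. With the pooled normal approximation, two-sided 5%:

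- 18 versus 42: pooled rate (0.6×18 + 0.2×42)/60 = 0.32; SE0 = √[0.32×0.68×(1/18+1/42)] = 0.1314; SE1 = √[0.24/18+0.16/42] = 0.1309; z = (0.4 − 1.96×0.1314)/0.1309 = 1.09; power 86.2%.
- 30 versus 30: pooled rate 0.40; SE0 = 0.1265; SE1 = 0.1155; z = 1.32; power 90.6%.

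Both are within 2 points of the stated values. They do not bear on timing.

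**Timing.** Date the habit to the week in which the run is completed (an assumption, and the natural reading of formed). Let the run end on day d of week k and the survey fall on day s of its week, with d and s from 1 to 7. The run starts on day d − 6, which is at most day 1 of week k.

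| SRBAI used | Before run | During run | After completion |
|---|---|---|---|
| Week k (day s) | 0 | 28 (s ≤ d) | 21 (s > d) |
| Week k−1 (day s − 7) | 28 (s ≤ d) | 21 (s > d) | 0 |
| Week k−2 (day s − 14) | 49 | 0 | 0 |

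These are counts of combinations, not probabilities. The previous-week result depends wholly on the survey day: the share falling during the run goes from 0/7 for a day-1 survey to 6/7 for a day-7 survey. In week 1 a run can be completed only on day 7, so the same-week survey always falls within it.

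**How far the run has gone.** Among the 28 same-week combinations that fall during the run, write g = d − s (0 to 6). There are 7 − g combinations for each g, and 7 − g run days have been reached, counting the survey day. The average is Σ(7 − g)²/28 = (49+36+25+16+9+4+1)/28 = 140/28 = 5 of 7 days.

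**Fisher test.** A run completed by the end of week 8 (day 56) is finished before either of the last two weekly surveys (weeks 9 and 10).

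**Illustration under pure reverse causation.** Assumptions, none from the protocol: 60 participants, 40% form a habit, completion day uniform on days 7–70, SRBAI between- and within-person SD 0.7 each (total √0.98 ≈ 1), SRBAI raised by a fixed shift from the first run day, no effect of SRBAI on habit, pooled logistic regression adjusted for week in place of isotonic regression, and 300 replicates. For the logistic models the table gives the percentage significant and positive; for the Fisher test, the percentage significant.

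| Shift | Same week | Previous week alone, survey day 1 / 4 / 7 | Fisher |
|---|---|---|---|
| 0 | 3–4% | 2 / 2 / 2% | 3–5% |
| 0.5 SD | 64–68% | 1 / 17 / 53% | 43–47% |
| 1.0 SD | 99% | 4 / 53 / 96% | 92–95% |

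Monte Carlo error is up to about 3 points.

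**Limit of a longer lag.** In a second simulation (SRBAI rising 1 SD per SD of that week's walking, no forward effect), week k−2 SRBAI was significant in 4.5% of 400 trials with identical participants. Adjusted for week, in 200 trials, the rate was about 8% with identical participants, 33% when walking propensity varied between people with a logit SD of 0.5, and 61% with 0.8. These rates depend strongly on the assumptions, but their direction is clear.

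**The case against.** The strongest defence is that the protocol orders predictors against the event, and the event is completion of the seventh day. On that reading a survey taken during the run does precede the outcome (28 of 49), and one taken after completion (21 of 49) is excluded by the rule against post-event SRBAI. What remains would be an ambiguity between a cut by week and a cut by event, which an analysis plan could settle. This stands in part: the two rules can be reconciled. But a survey taken when on average 5 of the 7 qualifying days have been reached is measured inside the outcome, and that order does not support a statement about what automaticity does to habit.

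Three stronger readings are tempting and are not supported:

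- *That previous-week SRBAI is also out of order.* It is never after the run, and it always precedes the run if the survey falls on day 1. The difficulty is that the survey day is unstated and that the lagged model still carries the same-week term.
- *That the Fisher test rests on the same false claim.* The time-order sentence concerns the weekly analyses only. The Fisher test is worded as an association and is valid for that; only a mechanistic use of it would be unsupported.
- *That the trial would confirm its mechanism almost regardless.* The high rejection rates come from assumed effect sizes and from logistic instead of isotonic regression. The protocol also calls the weekly estimates preliminary and isotonic regression a means to explore.

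**Conclusion.** The point holds in a limited form. The sentence on temporal order is wrong for same-week SRBAI if order is judged against the run that constitutes the habit (before the run in 0 of 49 combinations). Even judged against completion it can fail, because the formation week is included whole (after completion in 21 of 49). Previous-week SRBAI is sometimes affected, depending on the survey day. The Fisher comparison can show association but not mechanism, because for habits formed by week 8 the follow-up SRBAI is measured after the outcome.

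The timing result needs only the assumption that the habit is dated to the completion week; it depends on no effect size. The simulated rates only illustrate that the consequence could be large. This concerns secondary analyses, so the change should be made, but the primary habit-formation result is not threatened.

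**What to change.** 1. Correct the sentence on temporal order, state the survey day, and exclude any formation-week survey dated after the run was completed.
2. For directional statements, use one lag for every person-week that always precedes the run: week k−2 SRBAI for each week-k row, with baseline surveys for weeks 1 and 2. Omit the same-week term and adjust for baseline SRBAI. A uniform lag is preferable to choosing the last survey before the run, because person-weeks without a run have no first run day.
3. Report same-week SRBAI separately as a concurrent association.
4. State that the Fisher comparison shows association only. A landmark version may be added as a sensitivity analysis: SRBAI change from baseline to a fixed week against habit formed afterwards, among those who have not yet formed one.

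**Cost.** No new data are needed, since SRBAI is already weekly, and the wording can be settled before the analysis expected by Fall 2026. A short-lived effect of automaticity becomes harder to detect. The landmark analysis drops early formers, so the 86% and 89% power figures do not carry over to it. Lagging lowers reverse causation but does not eliminate it: people who walk steadily can raise their own SRBAI early and complete a run later, and baseline adjustment removes only differences already visible at baseline. The report should say so.

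### The joint and lagged isotonic models for automaticity and habit assume a non-decreasing SRBAI effect, so their SRBAI gradient alone is not evidence on the timing or lag of automaticity

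*Protocol article*

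**What the plan says.** The protocol article, under Secondary Outcomes and Analysis, sets out the question: "another secondary hypothesis of this trial examines the association between longitudinal behavioral automaticity and habit formation over time". Three steps follow.

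1. Univariate logistic regression of habit on SRBAI, taken at a given week.
2. A joint model, in which habit status "at a given week will be regressed on SRBAI in that week and the week number using multivariable isotonic regression".
3. A lagged version of the joint model, adding the previous week's SRBAI.

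Rows stop at the first week with a habit; otherwise, "if a habit is not formed, we will use SRBAI data in all 10 weeks". The article discloses that "isotonic regression assumes a monotonic association between habit (dependent variable) and the independent variables (SRBAI and time". For SRBAI it defends this as follows: "This assumption is reasonable because automaticity (as measured by the SRBAI) should increase proportionally as habit formation becomes more likely". For time it says "we also expect the association between habit and week number to be positive". It then presents the method as a data-led way of exploring how habit relates to SRBAI, on the ground that monotonicity is the only assumption made.

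The same section, for a separate secondary hypothesis, plans a 2-sided Fisher exact test, autoregressive models of order 1, and a mixed-effects logistic regression with automaticity, time and their interaction. The Discussion (Principal Results) says the trial "will help determine whether behavioral automaticity acts as the primary MoBC".

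**The concern.** The question is whether habit formation goes with automaticity over time, and with what timing. The only models that take SRBAI jointly with week, or with its lag, have the sign of that association built in, and the reason given for the sign is the hypothesis under study. Monotonicity is a mild assumption about shape. About direction, it is the decisive one.

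An upward SRBAI gradient from such a fit is what one would see whether or not automaticity matters. If it were read as showing how the timing of automaticity change affects habit, the reading would come largely from the constraint. The point concerns the SRBAI direction only, not the week-number direction.

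**Working it through.** The article gives no figure for the isotonic model, so there is none to reproduce. The check is what the fit returns when SRBAI has no relation to habit.

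**Inputs from the article.** Analysis sample of 60 and habit rates of 30% (null) and 50% (alternative), from Sample Size Calculation; 10 intervention weeks; rows cut at first habit. A sample of 80 is the number left after the expected 20% baseline attrition from 100.

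**Assumptions, not in the article.** The number of SRBAI levels (7 or 25), the within-person correlation of SRBAI, and the shape of the weekly habit hazard.

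**Event counts under a flat hazard.**
- Weekly risk giving 50% by week 10: 1 − 0.5^(1/10) = 0.067.
- Expected weeks at risk per person: 0.5 / 0.067 = about 7.5.
- n=60: about 448 person-weeks and 30 events. n=80: about 597 person-weeks and 40 events.

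**Why the fit leans upward.** With only a low and a high SRBAI group, with observed risks r_L and r_H, the non-decreasing least-squares fit has difference max(0, r_H − r_L). Downward noise is pooled to zero and upward noise is kept. With more SRBAI levels and 10 weeks there are many places for an upward step, so a wholly flat fit is possible but rare.

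**Simulation with no association.** SRBAI was autoregressive and independent of habit. The fit was a two-way least-squares isotonic regression, non-decreasing in SRBAI and week. The gradient is fitted weekly risk at high minus low SRBAI, averaged over weeks. There were 1000 trials per row (500 for 25 levels).

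| Scenario | Gradient > 0.5 point | Gradient > 2 points | Median (points) |
|---|---|---|---|
| n=60, 50% habit, flat hazard, 7 levels | 98.7% | 85.0% | 4.5 |
| same, 25 levels | 100% | 95.2% | 6.4 |
| same, 7 levels, rising hazard | 99.6% | 92.4% | 4.9 |
| same, 7 levels, falling hazard | 90.3% | 70.1% | 3.3 |
| n=60, 30% habit, flat hazard, 7 levels | 97.3% | 68.2% | 2.8 |
| n=80, 50% habit, flat hazard, 7 levels | 97.2% | 79.4% | 3.5 |

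The true difference is zero in every row. No fitted step in SRBAI was ever negative.

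A second simulation took SRBAI as a 1–7 mean score with between-person ICC 0.6 (200 trials per setting) and compared fitted risk at SRBAI 6 and 2. The gradient was above 0.1 point in 99.5% of trials at n=60 (mean 4.4 points) and in 100% at n=80 (mean 3.8 points).

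**Unconstrained comparator.** With no association, pooled logistic regression on SRBAI and week had a positive slope in about half of trials and a significantly positive one in 1 to 4%.

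**Truly inverse association.**
- Log-odds −0.2 per SRBAI level, n=60: isotonic gradient above 0.5 point in 89.1%; logistic slope positive in 6.5%.
- Log-odds −0.5 per SD: isotonic gradient positive in 85% (n=60) and 81% (n=80); logistic regression found the inverse effect in 73% and 88%.

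**Truly positive association.** With log-odds +0.3 per SRBAI level (n=60, 200 trials), the median isotonic gradient was 9.8 points, against 4.2 with no association in the same run. The size of the gradient therefore carries information, but only when set against what it would be with no association.

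**The case against.** The strongest reply is that unconstrained analyses of nearly the same question stand beside this one. The mixed-effects logistic regression models habit on automaticity, time and their interaction; the Fisher test is 2-sided; and General Statistical Analytical Approach gives regression coefficients 95% CIs and 2-sided P values. The automaticity comparison in Sample Size Calculation is the difference in habit rate by SRBAI increase, not the isotonic fit. All of this stands. A reader might infer that the trial cannot support or refute automaticity as the mechanism, and the article does not bear that out.

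It is also fair that the monotone assumption is disclosed, that the work is described as preliminary and exploratory, and that no rule makes an upward gradient count as a finding. The statistical analysis plan, not shown here, may hold a test or reference for the fit, so the lack of one is not the criticism.

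Two further over-readings should be avoided. The fit can come out flat, so it is wrong to say it can never show a null. And the percentages come from a least-squares isotonic fit written for this check, not from the named R package, under assumed inputs.

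What remains is that none of the unconstrained analyses is stated to include previous-week SRBAI or to stop at first habit, the device the article adopts so that predictors precede the outcome. The univariate logistic models take a given week and do not address the joint or lagged effect. The circular rationale and the data-led description are in the printed text, whatever the analysis plan adds.

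**Conclusion.** The point holds, confined to the joint and lagged isotonic models. With no true association, the model with SRBAI and week shows a positive average gradient in roughly 90 to 100% of simulated trials, against a true weekly risk of about 6.7% at 50% cumulative habit (3.5% at 30%: 1 − 0.7^(1/10)). The exact rate depends on the assumed SRBAI levels, hazard shape and habit rate. That the fit can never show an inverse relation depends on none of these. The lagged model carries the same constraint but was not simulated, so no rate is claimed for it.

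The isotonic gradient alone is therefore not evidence on the timing or lag of automaticity. The broader mechanism question can still be informed by the unconstrained analyses. This should be changed, but it does not threaten the primary analysis.

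**What to change.** In Secondary Outcomes and Analysis:

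- Add an unconstrained pooled discrete-time logistic model on the same person-week rows, with SRBAI, previous-week SRBAI and week as regressors, 2-sided at 5%, and name it as the inferential analysis of association.
- Keep the isotonic fit as a description of shape. Report its SRBAI gradient against a permutation reference: reassign whole 10-week SRBAI histories between participants, cut each at the recipient's event week, refit, and give the P value and the range under no association. The weekly survey runs through all 10 intervention weeks, so full histories exist apart from missed surveys.
- State that the direction of the isotonic fit is assumed and not found.

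The cost is wording and a little more computing, with no new data. The joint analysis may then report no association. The article expects data collection to finish by June 2026 and analysis by Fall 2026, so by that timetable the change can be made before analysis.

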### General Statistical Analytical Approach

Baseline measurements will be summarized with descriptive statistics, including mean, median, and SD for continuous variables (eg, age) and proportions for categorical variables (eg, sex). In regression models, all coefficients will be estimated with 95% CIs, and for the point estimates, 2-sided *P* values will be used. All analyses will be conducted as intent-to-treat using all available data for participants who receive the intervention. We will do multiple imputation using within-subject data during the intervention as a sensitivity analysis to handle missing data. For analyses of the primary outcome, missing step data will be assessed conservatively and will be marked as having the absence of the target behavior (eg, walking 250 steps each h during their preidentified, preferred 4-h period each day for 7 consecutive d) for that day or days.

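### The isotonic model's rising week effect is justified by cumulative risk, but rows that stop at the first habit week make it a model of the weekly hazard, which need not rise

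*Protocol article*

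**What the plan says.** All of this is in the protocol article under Secondary Outcomes and Analysis, unless noted.

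- **Outcome and covariates.** Habit attainment is the outcome: "binary yes or no) at a given week will be regressed on SRBAI in that week and the week number using multivariable isotonic regression". A second version adds the previous week's SRBAI.
- **Rows kept.** "This analysis will include data up to the first week where a habit is formed". A participant who never forms a habit contributes all ten weeks. After the event nothing is carried forward: "Once a habit is formed, we will not use SRBAI data after the event".
- **Constraint.** "isotonic regression assumes a monotonic association between habit (dependent variable) and the independent variables (SRBAI and time"). The article adds that the method assumes nothing beyond monotonicity and presents it as data-driven.
- **Reason for the week constraint.** Time as a covariate is said to indicate the cumulative "risk of forming a habit, we also expect the association between habit and week number to be positive".
- **Event.** Under Primary Outcome and Analysis, the habit is the target walking "each day for 7 consecutive days during the 70-day intervention period".
- **Purpose.** The analysis is to give preliminary estimates of how the timing of automaticity change affects habit.

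**The concern.** The argument about week number belongs to one quantity and the data layout to another. The proportion who have formed a habit by week w cannot go down. The probability of forming it in week w, among those who have not yet done so, can go up, stay level or go down. The rows described give the second quantity.

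Monotonicity is the only assumption the method makes, and half of it, the half for time, rests on this argument. If the hazard does decline, the fitted surface cannot show it. It pools the weeks instead, and the SRBAI effect, fitted jointly, is pooled with them. Timing is what the analysis is meant to inform.

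**Working it through.** The article gives no weekly habit rate, so there is no stated figure to reproduce. Step 1 rests on the text alone; steps 2 to 5 rest on assumptions stated there.

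**1. What the rows estimate.** A participant who forms a habit in week k contributes k − 1 zeros and then a one. A participant who never does contributes ten zeros. The mean outcome at week w is therefore

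h(w) = (first habits in week w) / (participants with no habit before week w),

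which is a discrete hazard. Cumulative risk is F(w) = 1 − ∏(1 − h(j)) over j ≤ w. F must be non-decreasing; h has no such restriction. For example, if 50% form a habit by week 10 at a constant hazard, h = 1 − 0.5^(1/10) = 6.7% every week. F climbs from 6.7% to 50% with no week effect at all.

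**2. A falling case (assumed).** Suppose 60% of participants can form the habit, at 16.4% per week, and 40% never do.
- F(10) = 0.6 × (1 − 0.836^10) = 50%.
- h(1) = 0.6 × 0.164 = 9.8%.
- h(10) = 0.6 × 0.836^9 × 0.164 / (0.4 + 0.6 × 0.836^9) = 3.8%.
- The non-decreasing fit, weighted by number at risk, is total events over total rows: 0.50 / 7.05 = 7.1% in every week.
- In repeated samples of n = 60 the fit rises on average from 6.6% to 7.8%, while the raw hazard falls from 9.7% to 3.8%.

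**3. Day-level model (assumed).** Daily success probability varies between people by a Beta distribution, with an optional common upward trend on the logit scale over 70 days. The event is the first run of 7 successful days. The fit is in week alone.

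| Assumption | Weekly hazard | Non-decreasing fit |
|---|---|---|
| Beta(2,2), no trend | 6.6, 9.1, 7.1, 5.5, 4.5, 3.8, 3.2, 2.9, 2.6, 2.4% | flat at 5.1% |
| Beta(1,1), no trend | falls | flat at 5.9% |
| Beta(3,2), no trend | falls after week 2 | flat at 8.4% |
| Beta(2,2), +0.5 logit | still falls after week 2 | flat at 6.5% |
| Beta(2,2), +1 logit | about level, 7.7 to 8.4% from week 4 | close from week 4 on |
| Beta(2,3), +1.5 logits | rises every week, 2.7% to 10.8% | reproduces it |

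In the first row the fit is 5.1/9.1 = 0.56 of the true value in week 2 and 5.1/2.4 = 2.1 times it in week 10. Week 1 is often below week 2 because it holds only one complete 7-day window.

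A separate grid calibrated to 50% by day 70 crossed between-person logit SD (0 to 2) with personal trend (−1 to +2 logits). After week 2 the hazard fell in 9 of 16 settings, was flat in 1, U-shaped in 1, and rose in 5.

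**4. The article's own planning rates.** Sample Size Calculation uses 60% and 20% habit formation by automaticity group. With a constant hazard within each group (assumed), these are 1 − 0.4^0.1 = 8.8% and 1 − 0.8^0.1 = 2.2% per week. The pooled hazard drifts from 5.5% to 4.5% (50/50 split) or from 4.2% to 3.4% (30/70). The flat fits, 5.0% and 3.8%, miss by at most about 0.5 percentage points. If the expected 25% attrition is kept in the rows as absence of habit, the falls are 5.5% to 3.3% and 4.2% to 2.6%. The article states that rule for the primary outcome ("missing step data will be assessed conservatively and will be marked as having the absence of the target behavior") and does not say that it applies here.

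**5. Joint fit with SRBAI (assumed falling hazards, five SRBAI levels).** Every SRBAI level became flat in week. The top level, truly 23.1% falling to 4.6%, was fitted at 12.7% throughout; the bottom, truly 3.9% falling to 1.4%, at 3.1%. The SRBAI ordering survived. The week 1 gap shrank from 23.1 − 3.9 = 19.2 points to 12.7 − 3.1 = 9.6 points, and the week 10 gap widened from 4.6 − 1.4 = 3.2 points to the same 9.6.

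**The case against.** The strongest reply is that the trial's theory predicts a rising hazard. The Introduction describes habit as built by repetition in a stable context, and the intervention is meant to raise the probability of success. A simulation with no personal trend leaves out that learning and falls by selection alone; changing the Beta parameters does not test the premise. This stands. A reader might infer that the hazard will fall, or that the fit will be wrong by a factor of two. The article supports neither: it gives no hazard, and the direction turns on the balance of learning and heterogeneity.

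It also stands that the Beta figures are for week alone, that SRBAI in the joint model may absorb part of the heterogeneity (or of an upward trend), and that under the planning rates without attrition the drift is small against the noise of about 30 events.

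The last reply is that other analyses leave the shape free: week-by-week logistic regressions, the mixed-effects logistic model with a time-by-automaticity term, and the Kaplan-Meier curves. They would help a reader notice a decline. They do not repair the isotonic fit, which is the analysis chosen to study SRBAI and week jointly, and they do not make the cumulative-risk argument fit its rows.

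**Conclusion.** The point holds as a mismatch between reason and model. The rows define a weekly hazard, the justification concerns cumulative risk, and the non-decreasing constraint on week is unsupported by the reason given. That much needs no assumption.

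The practical effect ranges from none, when the hazard rises, to a fit that erases a roughly fourfold decline (9.1% to 2.4%) under the no-trend Beta(2,2) case. A decline is plausible, given the heterogeneity the trial plans to study and the message and intervention fatigue named under Potential Limitations, but it is not established. The consequence is confined to a secondary analysis described as preliminary; the primary binomial test is untouched. The change is still worth making, because timing is what this analysis is for.

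**What to change.** 1. Correct the sentence: the week term describes the weekly chance of a first habit among those still without one, not cumulative risk.
2. Fit a discrete-time hazard with monotonicity imposed on SRBAI only and week left unconstrained, for example as a factor, grouped weeks or a low-degree spline.
3. If the two-way isotonic model is kept, at least report the raw weekly hazard and an unconstrained-week fit beside it.

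An alternative that comes to mind is to model habit formed by week w and keep everyone through week 10. It would need SRBAI values after the event, which the article excludes so that predictors precede the outcome, and is not recommended.

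The cost is a few more parameters for week, with about 0.5 × 60 = 30 expected events if half of the 60 form a habit, which favours grouped weeks or a spline over a ten-level factor. Some model code must change, since the constraint would apply to SRBAI alone. No data collection is affected.
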